### Eligibility

Participants are (former) patients with cancer and their relatives. Eligible participants (1) have experience with oncology consultations, as a (former) patient or relative; (2) are fluent in Dutch; (3) are at least 18 years of age, and (4) have access to the internet at their home computer to complete the survey and view a video vignette. Inclusion of (former) patients with cancer and their relatives is believed to maximize identification with the patient displayed in the video vignette intervention.

### Video Vignette Intervention

#### Video Vignettes

Eligible participants are randomized in equal proportions to view 1 of 12 video vignette interventions. Video vignettes are scripted, hypothetical scenarios of real-life (medical) consultations, which allow for the systematic variation of verbal and/or nonverbal behaviors across experimental conditions [48,54-63]. Video vignettes are preferred in health communication research when ethical or practical considerations prevent the manipulation of physician behaviors in clinical practice. Participants are asked to view and evaluate vignettes while imagining themselves to be the patient in the video, that is, participants act as *analogue patients* [61,62]. Several studies demonstrated the validity of this type of methodology [60-63] and show that video vignettes allow for good levels of experimental control through script standardization and manipulation checks. Formal guidelines for video vignette development proposed by Hillen et al [61] and van Vliet et al [62] are used in this study to enhance internal and external validity.

#### Scenario Development

The first author (NL) used existing recordings (n=12) [64] and 2 days of real-life observations of consultations between hemato-oncologists and lymphoma patients to develop a script of a prototypical treatment-related consultation in hematology. Additionally, instructional materials for patients and evidence-based publications about malignant lymphoma and, in particular, DLBCL, its treatment (R-CHOP), and possible side effects were consulted. The main side effects and complaints associated with DLBCL and its treatment, as derived from the literature, included fatigue, nausea, infections, and anxiety.

When possible, exact excerpts from the transcribed consultations and information materials were embedded in the basic script to enhance ecological validity. To further ensure realism of the script, the basic script was discussed and revised in several discussion rounds with the project’s lead hematologist (MJK). Furthermore, the script was role played by 2 medical communication researchers to test the natural flow of the dialogue. The basic script was then sent out for commentary to an expert panel consisting of 8 hematologists, radiotherapists, and oncologists from academic and regional hospitals, ranging in experience from resident in training to senior attending. Additionally, 11 patients with a history of lymphoma or blood cancer were recruited to provide written feedback. This was done via PanelCom [65], an online panel for patient-provider research. Expert panel members were subsequently excluded from further trial participation. Finally, a professional scriptwriter also commented on the script. The physicians, patients, and scriptwriter were asked to specifically provide feedback on the script’s (medical) realism and the interaction between the physician and patient. The script was revised accordingly and discussed for final revision by the overall project group, including 4 medical psychologists, 1 hematologist, 3 medical communication researchers, and 2 medical education experts.

#### Experimental Manipulations

The basic script was designed such that the independent variables of interest—structuring, tailoring, and caring—could be integrated into the dialogue in the form of blocks of text fragments. These fragments sometimes consisted of a turn-taking sequence between the hematologist and patient or of short utterances added to the hematologist’s text. Experimental manipulations were thus operationalized primarily as verbal expressions, which were in turn supported by nonverbal behaviors, if possible (eg, using hand signals to support statements such as “first,” “second”).

##### Structuring

On the basis of theoretical conceptualizations of text structuring [37,38,66,67], providing structure when giving information was operationalized (1) by having the physician provide verbal signals that introduce content and set the agenda (eg, “In today’s consultation I will tell you more about the treatment with chemotherapy and what to expect”; “I would like to discuss four possible side-effects and complaints with you”), (2) by having the physician summarize information (eg, “In short, you could thus suffer from nausea, fatigue, and infections”), and (3) by having the physician use ordinal or numeral text signals to indicate separate elements in a series (eg, “first, second”; “additionally, moreover, finally”). These structure markers were absent in the standard script (see Table 2).

##### Tailoring

Patients’ need for information was operationalized in the video script by having the patient respond to a prompt by the physician (eg, “Would you like to know more about this?”). The patient either confirmed a preference for more information (eg, “I would like to know as much as possible”) or stated that the information received was considered sufficient for the time being (eg, “It’s clear for now. I would like to let it all sink in”). This was done twice, once at the beginning and once toward the end of the consultation, keeping the patient’s need for information (high vs low) consistent across the script. Tailoring was defined as a match between a high information need of the patient and the provision of further information (*tailoring*^*+*
^) or a match between a low-information need of the patient and the absence of further information provision (*tailoring*^*−*
^). In contrast, lack of tailoring was defined as a mismatch between need for information and information provision (*no tailoring*^*+*
^ and *no tailoring*^*−*
^; see Table 2).

##### Caring

Physician caring was operationalized based on Hillen et al [33] who developed, tested, and used doctors’ verbal expressions of caring in a scripted video vignette study to test the effect of caring on trust. These verbal utterances were modified to fit the hemato-oncology setting, based on feedback from the expert panel, the patients, screenwriter, and project group during script development. The overall effectiveness of these manipulations of provider caring was established previously [33]. In the standard script, these expressions of caring were absent (Table 2).

##### Pretest Script Manipulations

To test the efficacy of the manipulations pertaining to information structuring and information preference tailoring, a pretest was conducted among a convenience sample of 63 participants (76%, [48/63] female; age range: 20 to 72 years; mean 41.5), including 19% (12/63) physicians (5 of which were hematologists), 11% (7/63) patients with lymphoma and blood cancer, 33% (21/63) researchers, and 37% (23/63) participants without previous experience in hemato-oncology. Participants were randomly assigned to one of the experimental conditions in which they were asked to read short, relevant excerpts of the script. Depending on the condition, participants were asked to rate the extent to which the physician *structured* the provided information or *adjusted* the amount of information to the patient’s personal needs on a scale from 1 (not at all) to 10 (a lot). In an open-ended question, they were asked to explain their judgment. The findings from the pretest suggested that these manipulations were largely recognized. Nonetheless, participants did not always correctly distinguish between structured and unstructured information provision. To resolve this, information structuring signals were made more explicit in the script, for example, by reformulating text fragments more strongly and by emphasizing verbal statements with nonverbal behaviors.

#### Filming and Editing

The roles of physician and patient were played by professional actors with ample experience as standardized patients in the medical context and with video vignette research in particular. The role of the hematologist was played by a 51-year-old white male; the role of the patient was played by a 57-year-old white female. The video vignettes were recorded by a professional film crew, over the course of 2 days, at our hospital. The first day of filming was used as a training day and resulted in a preliminary video clip, shot with a single-camera setup. This clip was shown to a group of 10 medical communication and education experts who provided feedback on, for example, aspects such as quality of the image, as well as the acting skills and realism of the set. Changes were made where necessary. On the second day of filming, the entire script was filmed using a multicamera setup: the scenario was shot from 3 different angles. Subsequent editing resulted in 12 experimental video vignettes, ranging in length between 9 and 11 min.

### Outcomes, Survey Development, and Testing

#### Survey (Outcome) Measures

As preparatory work for the trial, the experimental survey, including the study outcome measures, was developed and tested in a pilot study.

##### Background Measures

Survey questions concerning participants’ sociodemographic background included gender, birth year, ethnicity, living situation, educational level, and occupational status. In addition, questions concerning participants’ health literacy [68], medical knowledge (general and lymphoma-specific), overall health (1 item), and cancer (treatment and family) history were included. Personality trait measures included the avoidance scale of the Impact of Event Scale (8 items, 4-point scale) [69] to assess the tendency to avoid cancer-related issues, the Trait Anxiety Inventory (20 items, 4-point scale) [70] for the assessment of generalized anxiety, the Threatening Medical Situations Inventory (TMSI-2, Monitoring scale) [71] to assess a monitoring coping style, and a single item assessing information preferences in medical consultations (5-point scale).

##### Manipulation Checks

To assess manipulation success of the independent variables, 3 items similar to those used in the pretest were included (scale 1-10; perceived structuring, tailoring, and caring). Open text boxes were added for participants to explain their judgments. The Video Engagement Scale (15 items; 7-point scale) [60] was included to measure participants’ involvement with the video vignette.

##### Information Recall

Information recall was measured following the protocol of the Netherlands Patient Information Recall Questionnaire [8]. On the basis of the video vignette script, an item pool was developed, pairing open-ended questions (active recall) with analogous multiple-choice questions (recognition). A code sheet was developed by the authors (NL and ES) to assess correctly recalled items and calculate active recall and recognition scores. The results from the pilot test were used to refine the scale items. Two coders independently scored the pilot answers. In the case of disagreement, results were discussed to reach consensus (for further details, see pilot testing results below).

Participants’ *satisfaction with the information* provided in the video was measured with 7 single items (5-point Likert scale). In total, 4 items were taken from the European Organisation for Research and Treatment of Cancer Quality of Life Questionnaire-INFO25 survey (items 52-55) [72]. Items assessed participants’ satisfaction with the *content* and *amount* of information provided by the hematologists; their *desire for more* or *less* information; the perceived *usefulness* and *clarity* of the information; and their satisfaction with the hematologist’s *information giving style*. Participants were asked to explain their answer in an open-ended question box.

To assess participants’ *trust* in the video hematologist, the 5-item short trust in oncologist scale (5-point Likert scale) was added [73].

##### Expected Symptom Distress

*Expected symptom distress,* that is, the perceived probability (1=very improbable to 5=very probable), severity (1=not at all severe to 5=very severe), and controllability (1=very little to 5 a lot) of physical as well as emotional distress was measured using separate items for each of the possible complaints discussed by the hematologist (fatigue, nausea, infections, and anxiety). Hemato-oncologists whom we consulted for this study differed in their opinion as to whether patients would appreciate information about the possible evolution of anxiety. For this reason, we added a single item (1=very unimportant to 5=very important) to measure the extent to which participants find it important that hematologists explicitly discuss possible feelings of anxiety and insecurity following diagnosis and treatment.

On average, participants found the physician’s information structured (mean 8.13, range 3 to 10). They also deemed the amount of information provided by the physician quite adapted to the patient’s needs (mean 7.72, range 2 to 10). Finally, participants perceived the physician as relatively empathetic (mean 7.57, range 3 to 10). Owing to the small group sizes (n=3 per condition), between-group differences were not tested. However, these overall scores suggested the potential for ceiling effects in the item’s responses. Items were revised slightly to minimize these effects, but attention should be paid to this during the trial.

The recall instrument required revision (NL and ES), as some items appeared overly easy or complex. Adaptations resulted in a total pool of 28 items (14 active recall and 14 recognition). For active recall, possible scores now range from 0 to 33 for recognition from 0 to 14. The pilot test indicated sufficient variation for information satisfaction, physician trust, and expected symptom distress.

Taken together, the results of the pilot test and subsequent revisions support the start of the trial. The procedures of the planned trial are further detailed below.

### Participant Timeline

Participant recruitment and data collection are expected to last up to 2 months to reach the required sample size. This is considered feasible, based on previous experience using participant panels for study recruitment.

### Sample Size

The required sample size is estimated at N=420 participants (*structuring* N=180 and *tailoring* N=240), based on *a priori* power analyses in G*Power [75] with the alpha set at .05, a probability level of .80, and estimated medium effect sizes of .10 to .25 for the dependent variables, that is, information recall, information satisfaction, and trust in the physician.

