## Methods

### Trial Design

The trial employs a between-subjects single-message factorial design in which the independent variables of interest are systematically manipulated. This is done using the video vignette methodology. In experiment 1, hematologists’ information structuring and expressions of caring are varied in a 2 (standard versus enhanced structuring) × 2 (standard versus enhanced caring) design. In experiment 2, hematologists’ information tailoring and expressions of caring are varied in a 2 (high versus low need for information) × 2 (high versus low amount of information provided) × 2 (standard versus enhanced caring) design. This results in 12 experimental conditions, or interventions, across the trial (see Tables 1 and 2).

**Table 1 table1:** Experiment 1: Manipulation of provider information structuring and caring (2×2 design).

Manipulations	Standard of care	Caring
Standard of care	Standard of care	Enhanced caring
Structuring	Enhanced structuring	Enhanced caring and structuring

**Table 2 table2:** Experiment 2: Manipulation of provider caring and information tailoring in a match/mismatch design (2×2×2 design).

Manipulations		Provider			
		Enhanced caring		No caring	
		Additional information provision	No additional information provision	Additional information provision	No additional information provision

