### Analysis

Data will be cleaned in a stepwise procedure [76], including the identification of missing values because of dropout, standardization and normalization of data, and outlier analysis. Data will subsequently be analyzed using IBM SPSS statistical package. In the first step, it will be determined whether the experimental groups, within each of the 2 subexperiments of the trial, are indeed comparable in terms of participant characteristics, such as sociodemographics, personality traits, and disease history. If differences are found, these will be controlled for in subsequent analyses. Then, for each of the 2 experiments, one-way analysis of variance or covariance (when aspects need to be controlled for) will be conducted to test the effects of information structuring, information tailoring, and caring on information recall, satisfaction, and trust (H1, H2, and H3, respectively). Additionally, the interaction effect between caring and information structuring as well as tailoring will be added to these models (RQ1). It will be investigated to what extent patient characteristics moderate the hypothesized relationships (RQ3). If necessary, because of violations of the assumption of homogeneity of variance, Welch F statistic will be employed. Posthoc comparisons, using Bonferroni or Games-Howell, will be used as applicable, to create a better understanding of between-group differences. Finally, linear regression analyses will be used to assess possible relationships of information recall, satisfaction, and trust with expected symptom distress (RQ2). Significance levels are determined at *P*<.05.

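### The stated sample sizes give 80% power at the top of the effect-size range .10 to .25, but not at the bottom: at f=.10, power is about 16% to 34%

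*Protocol article*

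**What the plan says.** The Sample Size section of the protocol article states: "The required sample size is estimated at N=420 participants (*structuring* N=180 and *tailoring* N=240". The inputs are an a priori G*Power analysis "with the alpha set at .05", "a probability level of .80, and estimated medium effect sizes of .10 to .25 for the dependent variables". The probability level is read here as power. The dependent variables it lists are recall, satisfaction with information, and trust. The section names neither the effect-size metric nor the test, and does not say that the numbers apply to only part of the range.

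The Trial Design section fixes the cells. Experiment 1 is a "2 (standard versus enhanced structuring) × 2 (standard versus enhanced caring) design", so 4 cells. Experiment 2 is a "2 (high versus low need for information) × 2 (high versus low amount of information provided) × 2 (standard versus enhanced caring) design", so 8 cells. Under Analysis, for each experiment, "one-way analysis of variance or covariance (when aspects need to be controlled for) will be conducted", with the interaction of caring with structuring or tailoring added to the models.

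**The concern.** One sample size cannot be the 80% solution for both ends of a 2.5-fold range of effects. For a fixed test the required N grows roughly as 1/f², so the lower end needs about (.25/.10)² = 6.25 times as many participants as the upper end. Read at face value, the sentence promises 80% power throughout the range.

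Recall, satisfaction and trust make up the primary objective, and .10 is given as an estimated effect for these same outcomes. If the sentence stands, a non-significant result could be read as 80%-powered evidence against effects down to .10. The design cannot support that reading.

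**Working it through.** **Inputs.** Alpha .05, power .80, effect sizes .10 and .25, N=180 and 240 (Sample Size); k=4 and k=8 cells (Trial Design). Assumption: the effect size is Cohen's f, the usual G*Power input for ANOVA.

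**Formula.** For a fixed-effects ANOVA, the noncentrality is λ = N·f², the denominator df is N − k, and power is the probability that a noncentral F(df1, N − k, λ) exceeds the central 95% point. For the one-way omnibus test df1 = k − 1, that is 3 or 7. Each main effect and each interaction has df1 = 1. This includes the tailoring match, which is the need-by-provision contrast.

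**Step 1: reproduce the plan's figures (omnibus, f=.25).**
- k=4: smallest N with power of at least .80 is 179; in equal cells, 4 × 45 = 180.
- k=8: smallest N is 237; in equal cells, 8 × 30 = 240.
- At N=180, λ = 180 × .0625 = 11.25 and power is .804. At N=240, λ = 15.0 and power is .807.

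Both stated numbers match.

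**Step 2: power at the stated numbers over the range.**

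| f | N=180, omnibus (df 3) | N=180, 1 df | N=240, omnibus (df 7) | N=240, 1 df |
|---|---|---|---|---|
| .25 | .80 | .92 | .81 | .97 |
| .15 | .36 | .52 | .33 | .64 |
| .10 | .17 | .27 | .16 | .34 |

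At f=.10, λ is 180 × .01 = 1.8 and 240 × .01 = 2.4.

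**Step 3: N needed for 80% power at f=.10.** Omnibus: 1,095 (k=4) and 1,443 (k=8). One df: 787 per experiment.

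**Step 4: smallest f with 80% power at the stated numbers.** Omnibus: .249 and .248. One df: .210 (N=180) and .182 (N=240). For two equal halves the standardised difference is 2f, so the 1-df values are about .42 and .36 standard deviations, while f=.10 is .20.

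**Step 5: other readings of the effect size.**
- Eta-squared .10 (f=.333): power is at least .97, but the omnibus numbers would be 103 and 137.
- f² of .10 (f=.316): power is at least .95, but the omnibus numbers would be 114 and 151.
- d of .10 to .25 (f=.05 to .125): power runs from .07 to .49.
- r of .10: power is .16 to .34.

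None of these gives 180 and 240 as the required numbers, and the last two leave the lower end just as short.

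**Step 6: numbers per experiment under the stated allocation.** Allocation and Blinding gives a 1:1 ratio over 12 conditions, 4 of them in experiment 1 and 8 in experiment 2.
- 420 × 4/12 = 140 and 420 × 8/12 = 280: 1-df detectable f of .24 and .17.
- 470 randomised, if split equally: about 157 and 313, giving 1-df detectable f of about .23 and .16.

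The article does not report the actual split of the 470.

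**The case against.** The strongest defence is that the metric is unstated, a journal article need not list every G*Power input, and on the eta-squared reading the 80% statement holds over the whole range. The first part stands: Cohen's f is an inference. The eta-squared reading does not fit, though, because it would have required 103 and 137 participants rather than 180 and 240. Nor is this a matter of missing detail: the section states inputs and an output that do not agree.

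Two stronger readings are tempting, and the documents support neither.
- A reader might infer that the numbers are adequate only for an omnibus test at exactly f=.25. That describes where they come from, not what they deliver. Single-df effects have .92 and .97 power at f=.25 and keep 80% down to about .21 and .18.
- A reader might call it an error to size the trial on an omnibus test when H1 to H3 and RQ1 concern single-df effects. The Analysis section speaks of one-way ANOVA, so the calculation fits that wording. Where single-df effects are tested instead, the omnibus number is conservative at a given f, so no power is lost.

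It is also fair to say that data collection is complete, that 470 were randomised against 420 required, and that no design decision now depends on this sentence. That limits the remedy to the text. It does not make the statement correct. Even pooling all 420 for the caring main effect, which the plan does not do, gives only .53 power at f=.10.

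**Conclusion.** The power statement is wrong as written for the lower part of its range. N=180 and N=240 are the omnibus solutions at f=.25. Power falls below 80% under about f=.25 for the omnibus test, and under f=.21 (N=180) or .18 (N=240) for single-df main effects and interactions. At f=.10 it is .17 and .16 (omnibus) or .27 and .34 (single-df).

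Calling the whole range medium is also wrong. On the f scale .10 is conventionally small and .25 medium, and the two correspond to differences of .20 and .50 standard deviations.

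These figures assume Cohen's f, equal cells, alpha .05 without multiplicity adjustment, and the planned 180 and 240. Equal allocation over 12 conditions would move the single-df thresholds to about .24 and .17 for 420 participants, or about .23 and .16 for 470. None of these splits brings f=.10 near 80%: even with about 313 in experiment 2, single-df power there is about .42.

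**What to change.** Revise the Sample Size section as follows:

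1. Name the effect-size metric and the test behind each number. If it was Cohen's f=.25 with a one-way omnibus ANOVA over 4 and 8 cells, say so.
2. Replace the range .10 to .25 with the smallest effect detectable at 80% power for the tests of H1 to H3 and RQ1, and do not call .10 medium.
3. Compute that value at the actual number analysed in each experiment, not at 180 and 240 by default. Reconcile the 180/240 split with the 1:1 allocation over 12 conditions.
4. Add that effects near f=.10 are not powered and that null results on recall, satisfaction or trust do not exclude them.

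The cost is text and a short recalculation. No change to design, data or analysis is needed. The stated power becomes less favourable at the low end.
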